## Abstract

**Background::**

Cerebral aneurysm surgery has significant mortality and morbidity rate. Inflammation plays a key role in the pathogenesis of intracranial aneurysms, their rupture, subarachnoid hemorrhage and neurologic complications. Proinflammatory cytokine level in blood and cerebrospinal fluid (CSF) is an indicator of inflammatory response. Cytokines contribute to secondary brain injury and can worsen the outcome of the treatment. Lidocaine is local anesthetic that can be applied in neurosurgery as regional anesthesia of the scalp and as topical anesthesia of the throat before direct laryngoscopy and endotracheal intubation. Besides analgesic, lidocaine has systemic anti-inflammatory and neuroprotective effect.

Primary aim of this trial is to determine the influence of local anesthesia with lidocaine on the perioperative levels of pro-inflammatory cytokines interleukin-1β, interleukin-6, and tumor necrosis factor-α in plasma and CSF in cerebral aneurysm patients.

**Methods::**

We will conduct prospective randomized clinical trial among patients undergoing craniotomy and cerebral aneurysm clipping surgery in general anesthesia. Patients included in the trial will be randomly assigned to the lidocaine group (Group L) or to the control group (Group C). Patients in Group L, following general anesthesia induction, will receive topical anesthesia of the throat before endotracheal intubation and also regional anesthesia of the scalp before Mayfield frame placement, both done with lidocaine. Patients in Group C will have general anesthesia only without any lidocaine administration. The primary outcomes are concentrations of cytokines interleukin-1β, interleukin-6 and tumor necrosis factor-α in plasma and CSF, measured at specific timepoints perioperatively. Secondary outcome is incidence of major neurological and infectious complications, as well as treatment outcome in both groups.

**Discussion::**

Results of the trial could provide insight into influence of lidocaine on local and systemic inflammatory response in cerebrovascular surgery, and might improve future anesthesia practice and treatment outcome.

**Trial is registered at ClinicalTrials.gov::**

NCT03823482.

## Introduction

1

Cerebral aneurysms are relatively common in a general population with a prevalence of 3%. Existing treatment options include surgical and endovascular treatment, both accompanied by a significant disability and mortality rate.^[1]^ Pathophysiological mechanisms of aneurysm etiology, their growth and factors contributing to rupture with consequent bleeding are not fully known yet. Recent studies emphasize the key role of inflammation in pathogenesis of aneurysms, their rupture, subarachnoid hemorrhage (SAH) and early brain injury, spasm of cerebral vessels and delayed neurological deficit.^[2]^

The inflammatory response, measured by the increased levels of pro-inflammatory cytokines in plasma and cerebrospinal fluid (CSF), is present during and immediately after elective neurosurgical procedures, as well as in patients following cerebral aneurysm rupture.^[3–5]^ Activation of inflammatory response and cytokine release contributes to secondary brain damage and death of neurons, leading to poorer outcome. Cytokines are released from central nervous system (CNS) cells, such as microglia, astrocytes, endothelial cells of the brain and neurons, but also from activated leukocytes and lymphocytes that passed from systemic circulation through blood-brain barrier (BBB).^[6]^ Specifically, the extracellular adenosine triphosphate (ATP) released from injured brain tissue, as well as the presence of subarachnoid blood, causes proliferation, migration, and activation of the microglia. Activated microglia release various cytotoxic substances that can damage brain cells, including pro-inflammatory cytokines, interleukin (IL) 1β, tumor necrosis factor alpha (TNF-α), and interferon gamma (IFNγ). Released cytokines may pass through the damaged BBB and subsequently be detected in the blood. In addition, a systemic inflammatory response may be caused by brain injury, bleeding or ischemia.

Research show that inflammatory cytokine levels, such as IL-6 and TNF-α, in plasma and CSF of patients with aneurysmatic SAH correlate with the occurrence of neurological and infectious complications as well as with the treatment outcome.^[7,8]^

Lidocaine is local anesthetic and antiarrhythmic drug with other significant systemic effects, such as anti-inflammatory, neuroprotective and antimetastatic effects.^[9]^ In neurosurgical patient local anesthetics can be used for regional anesthesia of the scalp and before direct laryngoscopy and endotracheal intubation with the aim of maintaining hemodynamic stability and avoiding intracranial pressure increase. For this purpose, regional and intravenous administration of lidocaine are both already described.^[10]^

Lidocaine exerts significant anti-inflammatory effect. In animal research model, both inhaled and intravenous lidocaine, attenuated levels of TNF-α, IL-1β, and IL-6 in lungs.^[11]^ Another study showed that intravenous lidocaine increase the concentration of anti-inflammatory cytokine IL-10 in mechanically ventilated animal lungs.^[12]^ Clinical studies confirm that lidocaine, whether administered locally or intravenously, reduces levels of pro-inflammatory cytokines, although contradictory data exist.^[13,14]^

Recent research found significant effect of lidocaine on microglia. Lidocaine reduces the release of IL-1β and thus reduces the activation of the microglia as a key step of inflammatory response in CNS.^[15]^

The pharmacological modulation of the inflammatory process, which might be crucial in the pathology of cerebral aneurysms and treatment outcome, is still the subject of scientific research. The influence of local anesthesia with lidocaine during cerebral aneurysm surgery on inflammatory response as well as on the immediate postoperative period has so far not been systematically investigated.

We hypothesized that regional anesthesia of the scalp and topical anesthesia of the throat, both done with lidocaine, would significantly decrease the levels of pro-inflammatory cytokines in CSF and plasma of patients undergoing craniotomy and cerebral aneurysm surgery. Lower concentrations of pro-inflammatory cytokines might contribute to better outcome and might decrease the incidence of systemic and CNS related postoperative complications. Aim of this study is to determine the influence of lidocaine administration on perioperative inflammatory cytokine levels in plasma and CSF of patients undergoing craniotomy and cerebral aneurysm surgery.

## Methods

2

### Study design

2.1

This is an ongoing single center, prospective, randomized clinical trial at the University Hospital Center Zagreb, which is a referral hospital for cerebral aneurysm surgery and has case volume necessary for the study. Trial is registered at ClinicalTrials.gov (NCT03823482).

### Inclusion criteria

2.2

Patient scheduled to undergo craniotomy for cerebral aneurysm surgery under general anesthesia will be recruited for the trial. Inclusion criteria include age between 18 and 70 years, American Society of Anesthesiologists (ASA) physical status I-II and written informed consent.

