### Exclusion criteria

2.3

Patients with severe cardiovascular (New York Heart Association class 3 and 4) or pulmonary condition (Global Initiative for Chronic Obstructive Lung Disease class 3 and 4) will be excluded from the trial, as well as patients with ongoing acute infection or immunological disease. Patients on steroid treatment due to any reason will also be excluded. Patients with preoperative Glasgow coma score (GCS) lower than 15 or with significant motor deficit will also be excluded. Pregnancy and allergy to any of the medication used in study protocol are also considered to be exclusion criteria. Patients with significant intraoperative blood loss (more than 500 ml) or with prolonged surgery time (more than 6 hours) will be excluded from data analysis.

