### Randomization

2.4

Patients who meet the criteria will be randomly allocated to the lidocaine group or to the control group. Randomization will be computer generated with allocation ratio 1:1. Randomization and enrollment will be done by an independent physician who is not directly involved in the care of the patients. Anesthesiologist will not be blinded to the grouping, but the participants. Unblinding could be done in case of any medical emergency. In case of unblinding, the patient will be excluded from the trial. Allocation concealment will be ensured with closed envelop method, which cannot be opened until induction of the anesthesia have been completed

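### Eligibility leaves room for ruptured as well as unruptured aneurysms, but the stated between-group tests ignore rupture status, at a possible cost in power and chance imbalance with 20 per arm

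*Protocol article*

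**What the plan says.** Section 2.2 (Inclusion criteria) opens with "Patient scheduled to undergo craniotomy for cerebral aneurysm surgery under general anesthesia will be recruited for the trial" and continues "Inclusion criteria include age between 18 and 70 years, American Society of Anesthesiologists (ASA) physical status I-II and written informed consent". The nearest limit in section 2.3 (Exclusion criteria) is "Patients with preoperative Glasgow coma score (GCS) lower than 15 or with significant motor deficit will also be excluded". Neither section names rupture or subarachnoid haemorrhage, either to admit or to exclude it.

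The Introduction says that the inflammatory response, measured by raised cytokines in plasma and CSF, "is present during and immediately after elective neurosurgical procedures, as well as in patients following cerebral aneurysm rupture". It adds that extracellular ATP from injured brain, "as well as the presence of subarachnoid blood, causes proliferation, migration, and activation of the microglia", and that activated microglia release IL-1β, TNF-α and IFNγ. IL-1β, IL-6 and TNF-α in plasma and CSF are the primary outcome (section 2.7), and vasospasm is among the secondary outcomes (section 2.8).

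Section 3 (Statistical analysis plan) names Friedman's test with Dunn post-hoc comparisons, the Mann-Whitney test, Student's t test, Spearman correlation and ROC curves. It names no covariate and no stratum. Section 2.9 sets a minimum of 20 patients per group at α = 0.05 and β = 0.1.

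**The concern.** A patient operated on after a bleed and a patient operated on electively may start from different cytokine levels, and the protocol's own rationale gives the reason. If both kinds enter, rupture status is a prognostic factor known before randomisation and available in the chart. A crude two-group test leaves its variance in the error term and makes no allowance for a chance difference in ruptured share between two small arms.

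The stakes are lost power and a group difference that is harder to interpret if the arms turn out unequal. CSF is the weaker side. By section 2.5 its first sample is taken at incision, after both lidocaine applications, so no pre-treatment CSF value can show or absorb a difference in starting level. Plasma has a sample before induction.

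**Working it through.** **Inputs from the document.** 20 per group, α = 0.05, power 90% (section 2.9); 1:1 allocation (section 2.4). Sidedness is not stated; two-sided is assumed.

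**Assumed inputs, because the document gives none.** Ruptured share p = 0.2 to 0.5, with 0.1 as a low case. Shift Δ between ruptured and unruptured patients = 1 to 2 within-stratum SDs.

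**1. The plan's own figure.** No effect size or SD is stated, so 20 per group cannot be reproduced, only solved backwards: d = (1.960 + 1.282) × √(2/20) = 1.025 SD. A t-based calculation gives 1.05.

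**2. Chance imbalance.** Take the ruptured counts in the two arms as independent Binomial(20, p). The SD of the difference in share is √(2p(1−p)/20), for example √(2 × 0.3 × 0.7/20) = 0.145 at p = 0.3. The exact chance of a difference of 20 points or more (at least 4 patients) is:

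| Ruptured share | Chance |
|---|---|
| 10% | 6% |
| 20% | 16% |
| 30% | 23% |
| 50% | 27% |

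A 20-point gap moves the group difference by 0.2 × Δ, which is 0.2 SD at Δ = 1 and 0.4 SD at Δ = 2. Against d = 1.025 that is 20% and 39%.

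**3. Power of the crude test.** The total SD is s = √(1 + p(1−p)Δ²), and power = Φ(1.025/(s√(2/20)) − 1.96).

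| p | Δ | s | Power | n per group for 90% |
|---|---|---|---|---|
| 0.2 | 1 | 1.077 | 85% | 24 |
| 0.3 | 1 | 1.100 | 84% | 25 |
| 0.5 | 1 | 1.118 | 83% | 26 |
| 0.2 | 2 | 1.281 | 72% | 33 |
| 0.3 | 2 | 1.356 | 67% | 37 |
| 0.5 | 2 | 1.414 | 63% | 41 |

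At p = 0.1, s = √(1 + 0.09) = 1.044 at Δ = 1, giving 87%; s = √(1 + 0.36) = 1.166 at Δ = 2, giving 79%.

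This takes the planning SD to be a within-stratum SD. If it came from a mixed population, the 20 per group already carries the rupture variance, and the same figures describe a gain forgone rather than a loss.

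**4. CSF.** Drains are placed only when otherwise indicated (section 2.5). If 10 per arm had one (assumed), the chance of a gap of 20 points or more would be 39% at p = 0.2 and 50% at p = 0.5.

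**5. False positives.** Over all randomisations the error rate is preserved. Given an exact 20-point gap, simulated Mann-Whitney tests (20,000 runs each; Δ = 1 or 2; 8 against 4 or 12 against 8 ruptured) rejected a true null in 5.9% to 7.8% of runs.

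**The case against.** The strongest reply is that no sentence says ruptured cases will be enrolled. Scheduled surgery, ASA I-II, written consent, GCS 15, no significant motor deficit and no steroids all point to a mild, planned population. Monitoring for vasospasm fits with haemorrhage patients being in scope but does not establish it. This stands, and it makes the point conditional on who is recruited.

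A reader might also infer that the randomisation is at fault for not stratifying. The text says only "Randomization will be computer generated with allocation ratio 1:1". That does not rule out strata or blocks, and a condensed article may leave them to the full protocol. No fault in the randomisation is shown.

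A reader might infer that the protocol says rupture raises all three measured cytokines above their level in elective cases. It does not. The Introduction reports a response in both settings and gives no size of difference. Its subarachnoid-blood mechanism lists IL-1β, TNF-α and IFNγ; IL-6 in haemorrhage patients appears only as a correlate of complications and outcome.

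Finally, a reader might infer that an imbalance could not be told apart from a lidocaine effect. For plasma that goes too far, because the pre-induction sample would partly reveal it.

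What survives concerns the analysis. Section 3 commits to specific two-group tests, and none of them uses rupture status or the pre-induction plasma value as a covariate.

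**Conclusion.** The point holds in conditional form. The criteria do not keep ruptured aneurysms out, the rationale gives reason to expect rupture to matter for the primary outcome, and the stated tests ignore it. With 20-50% ruptured and a shift of 1-2 SD, the cost is a 16-27% chance of a 20-point or larger imbalance and a fall from 90% power to 83-85% or 63-72%. With about 10% ruptured, the imbalance risk is 6% and the power loss at 1 SD is about three points; only a shift near 2 SD would still matter much. Share and shift are both assumptions.

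The documents support a loss of precision and a weaker reading of any chance imbalance, mainly in CSF. They do not support a claim that the comparison is biased or the type I error broken. The change is worth making because the factor is known before treatment and the remedy is cheap.

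**What to change.** State whether ruptured aneurysms are eligible, and record rupture status (ruptured or unruptured) at enrolment. If both types are enrolled, replace the crude primary between-group comparison with one of two methods, fixed before outcomes are examined by arm:

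- a rank test stratified by rupture status (van Elteren), which stays closest to the planned Mann-Whitney test; or
- a linear model of log cytokine with treatment and rupture status, adding the pre-induction value for plasma.

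Report the outcomes by rupture status descriptively.

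The Mann-Whitney, Friedman and t tests take no covariate, so this changes the primary method rather than adding a term to it. It costs about one degree of freedom for rupture status, and one more in the plasma model for the pre-induction value. If few ruptured cases enter, little is gained. Because the trial is described as ongoing, the change belongs in the analysis, through the amendment route in section 2.12; stratifying the remaining envelopes would add little.

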### Exclusion criteria

2.3

Patients with severe cardiovascular (New York Heart Association class 3 and 4) or pulmonary condition (Global Initiative for Chronic Obstructive Lung Disease class 3 and 4) will be excluded from the trial, as well as patients with ongoing acute infection or immunological disease. Patients on steroid treatment due to any reason will also be excluded. Patients with preoperative Glasgow coma score (GCS) lower than 15 or with significant motor deficit will also be excluded. Pregnancy and allergy to any of the medication used in study protocol are also considered to be exclusion criteria. Patients with significant intraoperative blood loss (more than 500 ml) or with prolonged surgery time (more than 6 hours) will be excluded from data analysis.

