### Interventions

2.5

Patients included in the trial will be randomly assigned to the lidocaine group (Group L) or to the control group (Group C). Patients in Group L, following general anesthesia induction, will receive topical anesthesia of the throat before endotracheal intubation with 40 mg of lidocaine and also regional anesthesia of the scalp with 2% lidocaine in maximum dosage 4 mg/kg before Mayfield frame placement. Total dosage of lidocaine will be up to 400 mg. Regional anesthesia of the scalp will be performed using technique described in relevant literature.^[16]^ Patients in Group C will have general anesthesia only without any lidocaine administration. All patients will undergo craniotomy and cerebral aneurysm clipping surgery with preoperative placement of lumbar CSF drainage, when it is otherwise indicated neurosurgically.

Blood samples will be taken from every patient included in the study at four timepoints: before induction of the anesthesia (baseline), at the time of incision, at the end of surgery and 24 hours from start of anesthesia. CSF samples will be taken from lumbar CSF drainage system at 2 timepoints: at the time of incision and at the end of surgery. Concentrations of IL-1β, IL-6, and TNF-α in plasma and CSF will be measured using enzyme-linked immunosorbent assay (ELISA) specific for each cytokine, according to manufacturer instructions.

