### Sample size calculation

2.9

Based on previous studies, we performed a sample size estimation before recruitment with the power analysis module of STATISTICA software version 10.0 (StatSoft Inc., San Diego, CA), using α = 0.05 and β = 0.1.^[17,18]^ We determined that a minimum of 20 participants was required per group for pair-wise comparisons of our samples.

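### Dropping randomised patients from the analysis for blood loss over 500 ml or surgery over 6 hours means that the analysed groups are no longer the randomised groups

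*Protocol article*

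**What the plan says.** Section 2.3 (Exclusion criteria) of the protocol article ends its eligibility list with an analysis rule: patients with "significant intraoperative blood loss (more than 500 ml) or with prolonged surgery time (more than 6 hours) will be excluded from data analysis". The rule is not limited to any outcome.

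Section 2.4 (Randomization) says that the envelope "cannot be opened until induction of the anesthesia have been completed", and on blinding: "Anesthesiologist will not be blinded to the grouping, but the participants". It also removes from the trial any patient whose allocation is unblinded. Under section 2.5 (Interventions), Group L patients "following general anesthesia induction, will receive topical anesthesia of the throat before endotracheal intubation with 40 mg of lidocaine", followed by the scalp block before the head frame is placed. The same section samples blood from every included patient, including at the end of surgery and at 24 hours; CSF is also sampled at the end of surgery where a lumbar drain is in place.

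Section 2.9 (Sample size calculation) works "using α = 0.05 and β = 0.1" and arrives at "a minimum of 20 participants was required per group for pair-wise comparisons of our samples". Section 3 (Statistical analysis plan) names tests, but no analysis set that would offset the rule in 2.3.

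**The concern.** A patient is randomised, treated or not treated with lidocaine, operated on and sampled, and may then be removed because of how the operation went. Randomisation makes the two full groups comparable in expectation. It gives no such guarantee for the subsets whose operations stayed under 500 ml and 6 hours.

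Two links would turn this into bias. The first is between the exclusion events and the outcome. Section 1 (Introduction) says that bleeding or brain injury may provoke a systemic inflammatory response, so excluded patients plausibly have higher end-of-surgery and 24-hour cytokines, and plausibly more complications. The second is between arm and exclusion. The introduction describes local anaesthetic use in these patients "with the aim of maintaining hemodynamic stability and avoiding intracranial pressure increase", and the anesthesiologist, who manages blood pressure and fluids, knows the group.

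At stake are the primary cytokine comparison and all three secondary outcomes. If no allowance is made for exclusions, power is at stake too.

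**Working it through.** **1. Order of events.** Induction is completed and the envelope opened (2.4). Throat lidocaine is then given before intubation, and the scalp block before frame placement (2.5). Surgery follows. Blood loss and operating time accrue only during surgery, so both exclusion events come after allocation and after treatment.

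**2. The plan's own figure.** No effect size or SD is given, so 20 per group cannot be reproduced forwards. Solving backwards for a two-sided t-test (sidedness is an assumption) with n = 20 per group, α = 0.05 and power 0.90 gives a standardised difference d = 1.052. The normal approximation gives (1.960 + 1.282) × √(2/20) = 1.025.

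**3. Power if 20 per group are randomised and the rule then applies.** Non-central t with non-centrality d√(n/2), 2n − 2 degrees of freedom and d = 1.052. The exclusion rates are assumed.

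| Excluded | Analysed per group | Power |
|---|---|---|
| 0% | 20 | 90.0% |
| 10% | 18 | 86.6% |
| 15% | 17 | 84.5% |
| 20% | 16 | 82.1% |

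At 15%, n = 20 × 0.85 = 17. To keep 20 analysed, 20 / 0.85 = 23.5, so 24 per group, would have to be randomised. Extra patients restore power but do not remove selection.

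**4. Bias when the thresholds are applied identically in both arms.** Suppose a latent surgical severity, standard normal, correlates ρ with a cytokine (scaled to SD 1). Patients above a cut-off are dropped, the arm changes only the share p who cross it, and lidocaine has no effect on the cytokine. The mean of the retained patients is −ρ·k(p), with k(p) = φ(z_p)/(1 − p), where z_p is the upper-p normal quantile and φ the normal density.

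- k(0.20) = 0.280/0.80 = 0.350
- k(0.05) = 0.103/0.95 = 0.109
- Bias at 20% v 5% = ρ × (0.350 − 0.109) = 0.241ρ. That is 0.10 SD at ρ = 0.4 and 0.19 SD at ρ = 0.8.
- Bias at 20% v 20% = 0 for any ρ.
- With k(0.15) = 0.274, bias at 20% v 15% = 0.076ρ, or 0.03 to 0.06 SD.

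Simulation of this model with 20 randomised per arm gave two-sided false-positive rates of about 6% (ρ = 0.4) to 9% (ρ = 0.8) at 20% v 5%, and about 5% at 20% v 20%. The arm that loses more patients looks less inflamed than it is, so the direction depends on which arm that is.

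**5. The other mechanism: a hidden effect.** Suppose instead that the event itself raises the cytokine by 1.5 SD and nothing else differs. If events occur in 20% v 5% and all are dropped, the retained groups have equal means: bias under the null is 0 and the false-positive rate 5%. But the effect among all randomised patients, (0.20 − 0.05) × 1.5 = 0.225 SD, is then invisible to the analysis.

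The exclusion rates, ρ and the 1.5 SD are assumptions; the article gives none of them.

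**The case against.** The strongest defence is that nothing in the article shows exclusion to depend on arm. The haemodynamic aim in the introduction concerns the scalp block and intubation, not surgical bleeding or duration. Section 2.6 sets one blood pressure target range for all patients, and the article does not say that the surgeon knows the allocation. The thresholds are fixed numbers applied to everyone. If exclusion is unrelated to arm, the bias is nil. All of this stands. It limits what can be said about size, but it does not justify the rule: balance cannot be known in advance, and with 20 per group two or three patients make a gap of 10 to 15 percentage points. Even with balance, the result describes only operations that stayed under the thresholds.

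The rule might also be defended as removing variation due to surgical trauma. Randomisation already balances that in expectation, and conditioning on an event after treatment can undo the balance.

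A reader might infer three stronger things that the article does not support:

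- **That the rule removes the most inflamed patients.** No cytokine data by blood loss or operating time are given. The introduction makes it likely that patients with a high response are removed, no more.
- **That any difference in exclusion rates creates a spurious cytokine difference.** Step 5 of the working shows a model in which 20% v 5% creates none. A spurious difference needs severity that raises cytokines whether or not the threshold is crossed. Getting one from equal event rates would need the rule to be applied unevenly between arms, which the text does not say.
- **That the analysed number falls below 20 per group.** Section 2.9 calls 20 a minimum and does not say that excluded patients count towards it.

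**Conclusion.** The point holds as one of principle with a conditional size. As written, the rule removes randomised and treated patients on events that follow allocation, and nothing in section 3 offsets it. Because it governs the primary comparison and every secondary outcome, it should be changed before the data are analysed.

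The magnitude cannot be determined from the article. Bias ranges from nil, when exclusion is independent of arm, to about 0.1 to 0.2 SD under the assumed 20% v 5% exclusion and a correlation of 0.4 to 0.8; its direction is unknown. Against a design that needs a difference of about 1.05 SD for 90% power, that is modest but not negligible. An effect running through bleeding or duration could also be hidden. The fall in power to about 84.5% applies only if no more than 20 per group are randomised and 15% are excluded.

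**What to change.** - Delete the sentence on blood loss and operating time from section 2.3.
- State in section 3 that the primary analysis includes every randomised patient with a sample, in the allocated group, whatever the blood loss or operating time. Apply the same principle to complications and the Glasgow outcome scale.
- Report blood loss, operating time and the number of patients meeting each threshold by arm.
- Keep the set without these patients only as a labelled sensitivity analysis.
- Align the sentence in section 2.4 that removes unblinded patients from the trial, so that their available data are also analysed as allocated. Otherwise it contradicts the new analysis set.

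The cost is a wording amendment. The trial is under way and section 2.12 requires formal amendment and ethics committee approval for changes of this kind, so approval may be needed. Section 2.5 already samples every included patient, so no further data collection is required. The data will be somewhat more variable.
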